### Data analysis

We will present absolute numbers for enrolment, eligibility, and complete follow up. Descriptive statistics will be used to present student demographics, along with the mean, standard deviation, standard error of the mean, and 95% confidence intervals for primary and secondary outcome measures.

The primary analysis will be based on complete cases on a per-protocol analysis. It seems likely that some data may not be available due to voluntary withdrawal of participants, or drop-out through lack of completion of individual data items , unforeseen technical difficulties, and general loss to follow-up. Where possible the reasons for data ‘missingness’ will be ascertained and reported. The pattern of the missingness will be carefully considered and the reasons for non-compliance, withdrawal or other protocol violations will be stated and any patterns summarised. The primary analysis will investigate the fixed effects of the factorial combinations of branching and feedback on the primary outcome measures, performance in a standardised composite clinical reasoning assessment and a 15-item self reported evaluation. Analysis of covariance (ANCOVA) will be used to identify main effects, effect sizes, and interactions between the two independent design variables (feedback and branching). Blocking factors in the ANCOVA will adjust for the effects randomisation group, case ordering and recruiting centre, with student GEM status and gender as covariates. Tests from the ANCOVA will be two-sided and considered to provide evidence for a significant difference if p-values are less than 0.05 (5% significance level). Estimates of treatment effects will be presented with 95% confidence intervals. Students case preferences for learning and realism, and EViP will be evaluated using chi-squared tests for grouping factors case design and number.

We will determine the predictive validity of performance in the VP composite assessment, using one institution’s summative examination results, WMS. We will use the correlation coefficient (Pearson’s product–moment, *r*) to determine the effect size of any linear correlation between the VP scores and institution examinations.

A detailed statistical analysis plan (SAP) will be agreed with the trial management group at the start of the study, with any subsequent amendments to this initial SAP being clearly stated and justified. The routine statistical analysis will mainly be carried out using R (http://www.r-project.org/) and S-PLUS (http://www.insightful.com/). Results from this study will also be compared with results from other studies.

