**Methods/Design:**

This is a multi-centre randomised 2x2 factorial design study evaluating two independent variables of VP design, branching (present or absent), and structured clinical reasoning feedback (present or absent).The study will be carried out in medical student volunteers in one year group from three university medical schools in the United Kingdom, Warwick, Keele and Birmingham. There are four core musculoskeletal topics. Each case can be designed in four different ways, equating to 16 VPs required for the research. Students will be randomised to four groups, completing the four VP topics in the same order, but with each group exposed to a different VP design sequentially. All students will be exposed to the four designs. Primary outcomes are performance for each case design in a standardized fifteen item clinical reasoning assessment, integrated into each VP, which is identical for each topic. Additionally a 15-item self-reported evaluation is completed for each VP, based on a widely used EViP tool. Student patterns of use of the VPs will be recorded.

In one centre, formative clinical and examination performance will be recorded, along with a self reported pre and post-intervention reasoning score, the DTI. Our power calculations indicate a sample size of 112 is required for both primary outcomes.

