### Problem statement and hypothesis

The influence of different design features in a VP is under-researched, although they can significantly affect the time and cost of VP production. A research study in this area would be able to answer this research question.

We hypothesise that the two important independent VP design variables, branching (present or absent), and structured clinical reasoning feedback (present or absent) are likely to influence students clinical reasoning in cases, and their user experience in terms of realism, engagement and learning value.

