**Secondary Outcome measures**		
*Other metrics collected in electronic environment*	Time spent per case (seconds)	During the case, recorded automatically
	Time spent per node (seconds)	
	Number of nodes visited	
	Case completion percentage.	
	Time spent per question (seconds)	

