**WMS Only**		
*Validated self reported reasoning assessment (DTI)*	Baseline and Mean improvement	Immediately Pre-and post- intervention
*Summative assessment*	Written and clinical	1 week post intervention
*Formative assessment*	Written and clinical	End of the year

Student evaluation of each case will be collected using an electronic version of the EViP questionnaire, a fifteen item self reported evaluation. This explores exploring authenticity, professionalism, learning, and coaching through the case, using Likert scales with additional free text responses. Secondary outcome measures for each case are student’s patterns of use of the case, such as time taken per case, case completion rates, and time taken to complete individual decisions.

Additional data will be collected from one centre, WMS, to support the validity of the VPs as educational and assessment tools. This includes a pre- and post-test Diagnostic Thinking Inventory, a 41 item validated assessment of clinical reasoning ability [24]. Performance in summative and formative written and clinical assessments, measured one week following the VP case, and several months later will also be collected.

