Therefore 112 students would be required to detect the main effects and large interaction effect of branching and feedback on self-reported scores. To detect an interaction effect of the same order of magnitude as the expected main effects would require a total of 448 students. The pool of students available for recruitment into this study is large at the three centres (WMS, n~160; UBMS, n~400; KMS, n~150). Given unforeseen recruitment problems and some loss to follow-up, a target of 112 students should be easily achievable to quantify the main intervention effects (branching and feedback) which are the primary focus of the study, with increasing recruitment above this target providing increasing power to detect potential interactions between the main effects.

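### The primary analysis is fixed as per-protocol complete cases, so inclusion depends on completion, a post-randomisation outcome; no as-randomised analysis is stated

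*Protocol article*

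**What the plan says.** The Data analysis section of the protocol article fixes the population: "The primary analysis will be based on complete cases on a per-protocol analysis". It then lists why data may be missing: voluntary withdrawal, technical difficulties, general loss to follow-up and "drop-out through lack of completion of individual data items". Its commitment on missing data is descriptive: "The pattern of the missingness will be carefully considered and the reasons for non-compliance, withdrawal or other protocol violations will be stated". No analysis of students as randomised is mentioned.

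Three other places bear on this:

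- **Completion is an outcome.** Table 1 lists "Case completion percentage" among the secondary outcomes, and the text below the table repeats it ("such as time taken per case, case completion rates, and time taken to complete individual decisions").
- **The designs are expected to act on engagement.** The Problem statement and hypothesis section says that branching and feedback are likely to influence clinical reasoning and "their user experience in terms of realism, engagement and learning value".
- **Each student gives four records.** The abstract says: "All students will be exposed to the four designs". Each case carries a 15-item reasoning score and a 15-item EViP evaluation.

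On losses, Sample size determination says: "Given unforeseen recruitment problems and some loss to follow-up, a target of 112 students should be easily achievable".

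**The concern.** Whether a record counts as complete is settled after randomisation, while the student is working through a design. The trial measures completion and expects the designs to influence engagement. Restricting the primary analysis to completers therefore conditions on something the intervention may change, and the groups compared need no longer be those that randomisation made comparable.

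There is also a cost in information. With four records per student, deletion at student level would discard good scores because another case was missed. What is at stake is the precision of both main effects and, if low-scoring students abandon one design more than another, their direction.

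**Working it through.** **1. The plan's own sample size.** Inputs from Sample size determination: difference 0.8, SD 1.32 (key feature problems); difference 0.5, SD 0.93 (self-report); two-sided 5%, power 80%. The standardised effects are 0.8/1.32 = 0.606 and 0.5/0.93 = 0.538. A two-sample t-test needs 43.7 → 44 and 55.3 → 56 per level, so 88 and 112 in total. Both stated figures reproduce. Neither contains an allowance for missing data.

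**2. Loss of data.** The document gives no missingness rate. Let q be an assumed chance that any one case is incomplete, independent across the four. Student-level deletion keeps a fraction (1 − q)^4 of students; record-level deletion keeps 1 − q of records. From 112 students and 448 records:

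| q | students kept | records kept, student-level | records kept, record-level |
|---|---|---|---|
| 5% | 0.95^4 = 81% (91) | 365 | 426 |
| 10% | 0.90^4 = 66% (73) | 294 | 403 |
| 20% | 0.80^4 = 41% (46) | 184 | 358 |

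Student-level deletion thus discards 14%, 27% or 49% of the records actually observed (for example, 1 − 294/403 = 27%).

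**3. Precision.** Assume within-student correlation ρ = 0.5 and a score SD of 1. With four complete records per student, the SE of a main effect is √((1 − ρ)/n), where n is the number of complete students. For n = 91.2, 73.5 and 45.9 this gives 0.0740, 0.0825 and 0.1044. Generalised least squares on all observed records with a student effect gives 0.0690, 0.0714 and 0.0769. The ratios are 1.07, 1.16 and 1.36. Simulation of trials of this size gave up to 1.17 and 1.38 for the last two.

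**4. Missing items.** The two primary outcomes are analysed separately, so the relevant counts are 15 items per record and 60 per student for each outcome. With 0.5% random item non-response (assumed), 0.995^15 = 93% of records and 0.995^60 = 74% of students are complete. With 1%, the figures are 86% and 55%.

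**5. Selection.** Assume no true effect, and that a student abandons a branched case exactly when the score on it would fall in the lowest 15%; unbranched cases are always completed. Spurious branching benefit:

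- Record-level deletion, no student effect: the mean of a standard normal cut at its 15th percentile, φ(−1.036)/0.85 = 0.233/0.85 = **+0.27 SD**, whatever ρ is.
- Student-level deletion (simulated): **+0.11 SD** at ρ = 0.5, **+0.17 SD** at ρ = 0.3.
- All observed cases with a student effect (simulated): **+0.18 SD** at ρ = 0.5, **+0.23 SD** at ρ = 0.3.

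The design targets are 0.54 to 0.61 SD. A milder set of assumptions has completion about 90% unbranched and 70–73% branched, with branched completion rising with score at log-odds 0.25 to 1.0 per SD (ρ = 0.5). It gives 0.04 to 0.16 points with student-level deletion and 0.09 to 0.34 points with record-level deletion, against the 0.8-point target. If completion does not depend on score, the bias is 0.

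**The case against.** Several stronger readings are tempting, and the document does not support them.

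- **That one missed case or item removes all of a student's scores.** A reader might infer this from the term complete cases. The article does not say so. Outcomes are collected for each case, and an ANCOVA fitted to student-case records would drop only the incomplete ones. The student-level figures are therefore one of two readings.
- **That all 120 items must be present.** This would pool two outcomes that the plan analyses separately. A missing EViP item need not delete a reasoning score.
- **That the designs will distort completion.** Listing completion as an outcome shows that it is measured, not that it differs. At Warwick and Keele the cases are done in teaching sessions in a computer cluster, which makes selective abandonment less likely there; Birmingham uses self-study time.
- **That the trial will be underpowered.** The 112 is a minimum, and the stated pool is about 160 + 400 + 150 = 710. It also comes from a between-student formula, whereas every student sees all four designs; actual power depends on a within-student correlation that is not given.
- **That a mixed model cures the bias.** In the scenario above it is more biased than student-level complete cases, though less than record-level deletion without a student effect.

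The article also promises to report reasons for and patterns of missingness, and leaves detail to a SAP that is not shown. The absence here of item-level rules or sensitivity analyses is therefore not itself an error.

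These objections limit the size of the problem, but the point remains. The article itself fixes the primary population, inclusion depends on a measured post-randomisation outcome under either reading, and recruiting more students restores precision without removing selection.

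**Conclusion.** The point holds as a badly fixed primary analysis set, not as a demonstrated bias or an arithmetic error. The plan expects missing data, selects on completion and states no as-randomised analysis.

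The size depends on what complete means. Deletion by student costs about 19%, 34% or 59% of students at assumed per-case missingness of 5%, 10% or 20%. Deletion by record costs 5%, 10% or 20% of records. Bias is conditional on completion depending on both design and score. In the one-sided abandonment scenario it is roughly a fifth to a third of the target effect with student-level deletion, and about half with record-level deletion. The missingness rates, their independence, the correlations of 0.3 and 0.5 and the abandonment rule are all assumptions; the document supplies none of them.

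**What to change.** Reword the Data analysis section, and carry the same text into the SAP:

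1. Make the primary analysis as-randomised: every consented student with any scored case, each case analysed under its assigned design, using all observed cases in a model with a student effect, separately for each primary outcome.
2. Keep per-protocol complete cases as a secondary analysis. Define per-protocol, and say whether complete applies to the student or to the student-case record.
3. Pre-state sensitivity analyses for score-driven abandonment, because the change in step 1 gains precision and as-randomised inclusion but does not remove that bias. One should score unanswered reasoning items in a started case as incorrect. This suits the reasoning score only, since the EViP evaluation has no incorrect answer.
4. Report case completion by design beside the primary results, so that readers can judge whether selection is plausible.

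The cost is wording and slightly more analysis work. The case software already tracks decisions and performance, so no new data collection is needed.

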### Intervention and Independent design variables

The intervention consists of students completing four VP cases sequentially. Each case takes approximately 30 minutes to complete. The cases focus on four core clinical musculoskeletal areas. These are large joint arthritis, back pain, polyarthritis, and connective tissue disease. The 2x2 factorial study design means that any cases can be designed in four different ways. The four case designs are: A) not branched+ no-feedback; B) branched+ no feedback; C) not branched+ feedback; D) branched+ feedback. Students will use all four of the case designs during the research (see Figure 1).

The first variable is branching pathways through the VP, present or absent. There are four branching points with three choices through the thirty-minute case. This gives a possible 81 core pathways (3^4) through the case in a branched form. The linear case has a single core pathway, with participants being redirected back to the core pathway irrespective of the decision made, for example by feedback from a supervising clinician in the case. The second variable is the use of structured feedback to promote clinical reasoning skills, present or absent. This will be in a predetermined approach through the cases at five key points through the case, based on the ‘SNAPPS’ approach [20], systematic approaches to help Bayesian reasoning [21], and symptom categorisation [31].

Cases will be piloted and tested by healthcare professionals and a cohort of students in one centre prior to the study commencing. For the study, students will complete cases at WMS and KMS is in the form of sequential teaching sessions to students, taking place in a computer cluster. Students at UBMS will complete cases during allocated self-study time during their musculoskeletal block.

Other than the described independent variables we will control for other design variables highlighted in a critical literature review [2].

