### Outcome measures

The primary outcome measures in this study are the performance in standardised composite clinical reasoning assessment using validated tools, and a modified self reported 15-item evaluation, reviewing four domains. These will be completed both during and immediately following each case. The secondary outcome measures are engagement and patterns of use within the cases and collected from the online environment (see Table 1). For each case, the composite clinical reasoning assessment consists of validated assessment of clinical reasoning. These 15 items are eight ‘key feature problem’ questions, one Bayesian reasoning question, two multiple choice questions on diagnosis, and four multiple choice clinical decision questions. For each case the content of these 15 items is identical, allowing comparison between case designs. This allows comparison of a case which is not branched with no structured feedback vs. the same case in a branched format with structured feedback.

**Table 1 T1:** Outcomes Measured during the study

***Institution***	***Outcomes for individual cases***	***Timing***

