### Sample size determination

The authors agreed an important educational effect of a 5% difference in the score on validated assessments of clinical reasoning skills, and student self reported evaluations score. As no gold standard exists for the measurement of clinical reasoning skills, we have based the sample size calculation on performance for clinical reasoning on performance in the key feature problems (KFPs) integrated into each VP case. A previous study has shown mean KFP scores in a student population to be approximately normally distributed, with a standard deviation of 1.32 [32]. In this study where we will use 16 KFPs, a 5% difference in scores is considered significant, that is a difference in mean scores of 0.8, corresponding to a standardised effect size of approximately 0.6 (moderate to large). Based on these assumptions, we would require a total sample size of 88 students to detect this difference with 80% power at the (two-sided) 5% level. Assuming the effect size to be the same for both branching and feedback interventions, a sample size of 88 students would provide sufficient power to detect the main effects and an interaction effect that was twice as large as the assumed main intervention effect in the setting shown in Table 2.

**Table 2 T2:** Sample size calculation for Key Feature Problems outcomes, and student self evaluation scores

**Key Feature problems**					**Student self reported Evaluation scores**				
		Branching		*Total*			Branching		Total
		No	Yes				No	Yes	
Feedback	No	22	22	*44*	Feedback	No	28	28	*56*
	Yes	22	22	*44*		Yes	28	28	*56*
*Total*		*44*	*44*	***88***	*Total*		56	*56*	***112***

If the interaction between branching and feedback interventions is of same order of magnitude as the expected main effects then we would require a fourfold increase in the sample size to give a total of 352 students. [33]

For self-reported scores, where a previous study reported a standard deviation of 0.93, [34] a 10% difference in scores (with a maximum of 5) is considered significant, that is a difference in mean scores of 0.5, corresponding to a standardised effect size of approximately 0.5 (moderate). Based on these assumptions, we would require a total sample size of 112 students to detect this difference with 80% power at the (two-sided) 5% level (Table 2).

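### The primary ANCOVA lists no student term although each student gives four scores, so the standard errors for branching, feedback and their interaction would be overstated

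*Protocol article*

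**What the plan says.** The design is crossed within student. The Abstract (Methods/Design) says "All students will be exposed to the four designs", and the section on the intervention and design variables says "Students will use all four of the case designs during the research". Both primary outcomes, the 15-item reasoning score and the 15-item self-reported evaluation, are collected case by case: "These will be completed both during and immediately following each case" (Outcome measures).

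Data analysis names an ANCOVA as the primary model for the two main effects and their interaction, and it lists the other terms: "Blocking factors in the ANCOVA will adjust for the effects randomisation group, case ordering and recruiting centre", "with student GEM status and gender as covariates". The decision rule is "Tests from the ANCOVA will be two-sided and considered to provide evidence for a significant difference if p-values are less than 0.05", and treatment effects are to be given with 95% confidence intervals. Neither a student block, a random student effect, a repeated-measures structure nor a clustered standard error is mentioned. The section closes by deferring detail to a statistical analysis plan, which is not shown.

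Table 2 (Sample size determination) puts 22 or 28 students in each of the four design cells, as if each student gave one score in one cell.

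**The concern.** Four scores from one student share that student's ability, or leniency as a rater. In a crossed design this shared part cancels out of the comparison between designs, so it should not count as error when branching and feedback are tested. The natural block is the student, and it is missing from the list of blocks.

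The listed terms cannot replace it. Randomisation group, centre, GEM status and gender remove differences between sets of students; differences between individuals within those sets go into the residual. The intervals for the primary contrasts would then be wider than the data justify and would not have their stated coverage, and the tests would run below their stated level.

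**Working it through.** **Inputs.** From the protocol: four scores per student, one per design; two-sided 5% level; 80% power; difference 0.8 with SD 1.32 and 88 students for key feature problems; difference 0.5 with SD 0.93 and 112 students for the self-reported score. Assumptions: within-student correlation ρ of 0.2, 0.3, 0.5 or 0.7 (not given), and a balanced Latin-square allocation of designs to cases (the flow diagram is not shown).

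**The plan's own figures.** The protocol says "we would require a total sample size of 88 students to detect this difference with 80% power at the (two-sided) 5% level". With d = 0.8/1.32 = 0.606, a two-sample comparison of independent students needs 86 in total by the normal approximation and 88 by the t-test. With d = 0.5/0.93 = 0.538 it needs 110 and 112. Both stated sizes reproduce as a parallel-group calculation with one score per student.

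**Standard errors.** Let s be the total SD and N the number of students.
- True SE of a main effect, taken within student: s√((1−ρ)/N).
- SE reported when 4N scores are analysed without student: 2s/√(4N) = s/√N.
- Ratio: 1/√(1−ρ) = 1.12, 1.20, 1.41, 1.83 for the four values of ρ.
- Actual level of the nominal 5% test: 2·P(Z > 1.96/√(1−ρ)) = 2.8%, 1.9%, 0.6%, 0.03%.

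**Check by simulation.** 4,000 runs with N = 112, fitted with all the listed terms, with and without student. SEs are in units of s and are alike for branching, feedback and the interaction (each coded ±0.5).

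| ρ | SE as listed | SE with student | Overstated by about | Actual level of 5% test |
|---|---|---|---|---|
| 0 | 0.095 | 0.095 | 0% | 5% |
| 0.2 | 0.094 | 0.084 | 12% | 2.8% |
| 0.3 | 0.094 | 0.079 | 19% | 2.0% |
| 0.5 | 0.093 | 0.067 | 40% | 0.6% |
| 0.7 | 0.093 | 0.052 | 78% | 0.04% |

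With student in the model the level is about 5% throughout. The simulated inflation is slightly below the formula at high ρ because the between-student terms absorb a little of the variance. With 20% of case scores missing at random, the SE is still overstated by about 13% (ρ = 0.3) and 28% (ρ = 0.5).

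**Power.** For a true effect of d (in SD units):
- as listed: Φ((d√N − 1.96)/√(1−ρ));
- with student: Φ(d√N/√(1−ρ) − 1.96).

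*Planned main effects.* d√N = 0.538 × √112 = 5.69, and 0.606 × √88 = 5.69. Already at ρ = 0 this gives Φ(3.73), above 99.9%, and power is higher for larger ρ. Power is above 99.9% with or without student.

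*A 5% difference on the 5-point self-reported scale.* The sample size section opens by calling 5% important for both outcomes. That is 0.25 points, d = 0.25/0.93 = 0.269, and d√112 = 2.845.
- ρ = 0.3: as listed Φ(0.885/0.837) = Φ(1.06) = 85%; with student Φ(3.40 − 1.96) = Φ(1.44) = 93%.
- ρ = 0.5: as listed Φ(0.885/0.707) = Φ(1.25) = 89%; with student Φ(4.02 − 1.96) = Φ(2.06) = 98%.

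*Interaction.* A difference of differences of 0.538 SD, as large as the planned main effect, is a coefficient of 0.269 on the ±0.5 scale. Its power figures are therefore the same: 85% against 93%, and 89% against 98%.

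**The case against.** **The student term may be in the analysis plan.** Data analysis speaks of fixed effects of the design combinations, which does not exclude a student error stratum, and a condensed article often leaves the error structure to the analysis plan. This stands in part: a reader might infer that the protocol commits to treating all scores as independent, and it does not say so. But the article is not silent on the model. It lists blocks and covariates and leaves out the block that the design calls for, and Table 2 has the same gap.

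**The planned effects are safe.** This stands in full. A reader might infer that a real branching or feedback effect of the planned size could be missed. The protocol's figures do not support that. The sample size assumes SE 2s/√N, and even the model as listed has SE s/√N, half of that. Large losses can be produced by choosing effects for which the student model has exactly 80% power: the listed model then has 68%, 51% and 22% at ρ = 0.3, 0.5 and 0.7. At N = 112, however, those effects are only about 0.22, 0.19 and 0.14 SD, well below the planned 0.5 to 0.6 SD.

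**The error is conservative.** This also stands. A reader might infer that repeated scores inflate false positives. For the design effects the opposite holds. SEs for centre, GEM status and gender would be too small, by a factor √(1+3ρ) = 1.38, 1.58 and 1.76 at ρ = 0.3, 0.5 and 0.7, but these are adjustment terms and no hypothesis test on them is planned.

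**ρ is unknown and the four topics differ.** This is fair, and it is why 0.2 is in the range. The error vanishes only at ρ = 0, which is implausible for repeated scores from one student.

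**Conclusion.** The point holds as a fault in how the primary model is specified. Fitted as listed, the ANCOVA overstates the SEs of branching, feedback and their interaction by about 12% to 78% for ρ from 0.2 to 0.7, so the 95% intervals are too wide and the 5% tests are conservative. The practical loss is in precision and in power for small effects and for the interaction, typically 8 or 9 percentage points in the examples above. The planned main effects and the validity of a positive finding are not threatened. The size rests on the assumed ρ, a balanced allocation and a common correlation between cases. It should be fixed, as a free gain in calibration and precision.

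**What to change.** State the primary model as a linear mixed model. Fixed effects: branching, feedback, their interaction, topic/case order, randomisation group, centre, GEM status and gender. Random effect: student. Alternatively, for complete data, use a repeated-measures analysis with student as the error stratum. Either way, test the three design effects against within-student error. If student is instead entered as a fixed block, it absorbs group, centre, GEM status and gender, and the plan should say so. Reconcile Table 2 with the crossed design by noting that every student contributes to all four cells.

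The cost is a sentence in the analysis section and one more term in R, which is already the planned software. No new data or extra recruitment are needed. The change should be recorded before the outcome data are analysed.

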**All institions (WMS, KMS, UBMS)**		
**Primary Outcome Measures collected for each VP**		
*Validated clinical reasoning assessments.*	Key Feature Problems score (x/8)	Student completes during the case
	Clinical Decision (x/4)	
	Bayesian Statistical Question (x/1)	
	Working diagnosis (x/2)	
	(Total score x/15)	
*Self reported evaluation (EVIP)*	*EViP Questionnaire (multiple domains)*	After each case
	*Case Preference: reasoning (n from 4) learning (n from 4)*	On completion of all cases
	*Preference of case (learning)*	
	*Preference of case (realism)*	

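### Chi-squared tests of EViP by case design ignore that each student gives four ordered ratings, and they sit beside an ANCOVA of the same primary outcome without a rule for which decides

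*Protocol article*

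**What the plan says.** In the Protocol article, Intervention and Independent design variables, the four case designs are the combinations of branching and feedback, and "Students will use all four of the case designs during the research". Table 1 lists the EViP questionnaire under "Primary Outcome Measures collected for each VP", completed after each case. The case-preference questions are listed in the same block but are collected once, when all cases are finished. The text after Table 1 says that EViP is collected "using Likert scales with additional free text responses".

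The Data analysis section names the primary outcomes as "performance in a standardised composite clinical reasoning assessment and a 15-item self reported evaluation" and gives both to an ANCOVA for the main effects and interaction of branching and feedback. On the model terms it says: "Blocking factors in the ANCOVA will adjust for the effects randomisation group, case ordering and recruiting centre, with student GEM status and gender as covariates". Later in the same paragraph comes the sentence at issue, which starts with the case preferences (learning, realism) and continues: "and EViP will be evaluated using chi-squared tests for grouping factors case design and number".

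**The concern.** A table of case design by response category holds every student four times, once in each row. Pearson's chi-squared takes its reference distribution from independent observations, and here the design rules that out.

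Three further features fit the study poorly:
- The test treats ordered Likert categories as nominal.
- Case design has four levels, so a significant result does not say whether branching or feedback is responsible, although the Sample size determination section calls those main effects the primary focus.
- The paragraph gives EViP two methods and does not say which one settles the outcome.

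At stake is mainly what is claimed from the chi-squared tests, most likely at item or domain level. A modest design effect on EViP could give a non-significant chi-squared result because the test does not suit the data. A reader would then have two unranked results for one primary outcome.

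**Working it through.** **Inputs from the protocol.** Four ratings per student, one per design. 112 students for the self-reported outcome. SD 0.93, maximum score 5, two-sided 5% level. The Sample size determination section gives two differences for self-reported scores: 5% as an important educational effect, and 10% for the calculation.
- 5% of 5 = 0.25 points; 0.25 / 0.93 = 0.27 SD.
- 10% of 5 = 0.5 points; 0.5 / 0.93 = 0.54 SD.

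**Assumptions, not in the protocol.** Within-student correlation ρ from 0 to 0.7. A single 5-category item with latent mean 3.5 and SD 0.93, rounded and limited to 1–5. A branching effect only.

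**The plan's own figure.** Per level, n = 2(z₀.₉₇₅ + z₀.₈₀)² × SD² / difference² = 2 × (1.960 + 0.842)² × 0.93² / 0.5² ≈ 54.3, so 55 per level and 110 in total. The t-based version gives 110.6. Rounded up to four equal cells of 28, this is the stated 112, and power at 56 per level is 81.2%. The figure reproduces, but it refers to a comparison of means. The protocol gives no power figure for the chi-squared tests.

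**Direction of the error.** For two designs rated by the same N students, the variance of the difference in mean rating is 2σ²(1 − ρ)/N. A test that assumes independence uses 2σ²/N. With ρ > 0 the assumed variance is too large, so the test rejects too rarely.

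**Simulation.** 112 students × 4 ratings, 3000 runs per setting. The Monte Carlo standard error is at most √(0.25/3000) = 0.9 percentage points. The 4×5 chi-squared has (4 − 1)(5 − 1) = 12 degrees of freedom. The Friedman test and the repeated-measures F have 3 for design; both are omnibus tests across the four designs, so they are fair comparators.

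| ρ | Type I error, chi-squared 4×5 | Type I error, Friedman | Power at 0.25: chi-squared | Friedman | Repeated-measures F | Power at 0.5: chi-squared |
|---|---|---|---|---|---|---|
| 0 | 4.7% | 4.7% | 36% | 55% | 59% | 97% |
| 0.3 | 2.7% | 4.7% | 29% | 70% | 75% | 98% |
| 0.5 | 1.4% | 4.9% | 22% | 84% | 86% | 98% |
| 0.7 | 0.3% | 5.4% | 13% | 97% | 97% | 99% |

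A separate run of the same comparison gave a chi-squared type I error of 2.3% / 2.0% / 0.7% at ρ = 0.3 / 0.5 / 0.7. Power at 0.25 points was 28% / 21% / 15% for chi-squared against 68% / 85% / 95% for Friedman, and 33% against 57% at ρ = 0. Power at 0.5 points was again 97–99%. The two runs agree within a few percentage points.

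**Where the gap comes from.** At ρ = 0 the gap to Friedman is 55 − 36 = 19 percentage points. It reflects ignored order and the extra degrees of freedom. At ρ = 0.5 it is 84 − 22 = 62. Of the added 43, 36 − 22 = 14 come from chi-squared becoming conservative, and 84 − 55 = 29 are precision that the within-student test gains and chi-squared forgoes.

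**A smaller table.** If the ratings are collapsed to branching yes/no (2×5), chi-squared has 51–55% power at 0.25 points over ρ = 0 to 0.7, against 76–99% for the within-student branching contrast.

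**The case against.** The strongest reply is that chi-squared does not carry the EViP conclusion. The same paragraph gives the 15-item evaluation to ANCOVA, with effect estimates and 95% confidence intervals, and those would be reported whatever the chi-squared tests show. This stands. A reader might infer that real differences in EViP would be reported as absent; the protocol does not support that. The ANCOVA is not a complete answer either, because its listed terms name no student effect and nothing says that it takes precedence.

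A reader might also infer that the tests produce false positives, or that they always lose most of their power. Neither holds. With positive correlation the test is conservative. At the 0.5-point difference used for sizing it keeps 97–99% power. The loss is severe at 0.25 points, which the protocol also calls important, and it depends on a correlation that the protocol does not give.

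Comparing the 12-df table with a 1-df contrast aimed at the one active factor would exaggerate the loss. At 0.3 SD, with a different set of category cut-points, such a comparison gives 31–33% against 98% at ρ = 0.5, but already 43% against 85% at ρ = 0. The omnibus comparison above avoids this.

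Finally, the sentence is brief. It does not say that the tables are 4×5 by item, or that design and case number are tested separately. Table 1 places the preference questions in the EViP block, so the sentence may partly concern those single-answer items, where chi-squared is reasonable. But it names EViP in addition to the preferences, and the independence problem arises in any chi-squared table that pools a student's four ratings. The choice of test is stated here, so it is not a detail left to the SAP.

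**Conclusion.** The point holds in limited form. As written, the chi-squared tests of EViP do not match a design in which each student gives four ordered ratings, and they duplicate the ANCOVA of a primary outcome without a ranking.

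For a 4×5 table from 112 students with ρ between 0.3 and 0.7, the actual type I error is about 2–3% falling to below 1%. At 0.25 points, power is roughly 13–29%, against 68–97% for an omnibus within-student test. At 0.5 points there is little practical loss. The non-independence itself is certain from the design. The sizes rest on the assumed correlation, item distribution and table layout.

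The consequence is missed modest effects and an ambiguous primary result, not spurious findings. It deserves correction before analysis, but it does not undermine the trial's main EViP analysis.

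**What to change.** Replace the chi-squared sentence with three statements:
1. Chi-squared tests are used only for the case-preference questions in which each student gives one answer.
2. EViP items or domains are analysed with a within-student ordinal method, for example a cumulative-link mixed model with branching, feedback, their interaction and case as fixed effects and a random student intercept.
3. The factorial ANCOVA-type model of the EViP score, with a student effect added to the listed terms, is the analysis that decides the primary EViP outcome. Item- and domain-level results are supportive.

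A random student intercept lets the listed between-student terms (randomisation group, centre, GEM status, gender) stay in the model.

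The cost is a few lines of text and slightly more analysis work in R, which the protocol already names. No change to data collection or sample size is needed.
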